The overall aim of the proposed research is to evaluate two different strategies for delivering HIV care and treatment services during the postpartum period to eligible HIV-infected women who initiate antiretroviral treatment (ART) during pregnancy and their HIV-exposed infants. The study’s primary objective is to compare an MCH-focused ART service to general adult ART services as strategies for providing ART during the postpartum period. The primary outcomes are (i) maternal HIV viral suppression, and (ii) maternal retention in ART services, at 12 months postpartum. Additional objectives focus on understanding the PMTCT ‘cascade’ (including the drop-out of ART-eligible women before delivery); investigating breastfeeding practices in the context of maternal ART use; MTCT rates at different times postpartum; and the acceptability and cost-effectiveness of the postpartum ART strategies under evaluation.

The study is to be conducted at the Gugulethu Midwife Obstetric Unit (MOU) in Cape Town. The study design has three interrelated phases.

- **Phase 1** is a cross-sectional evaluation of consecutive HIV-infected pregnant women seeking antenatal care at the study clinic (up to n=1600)
- **Phase 2** of the study is an observational cohort of all women from Phase 1 who are eligible for initiation of ART (up to n=600), followed in three study measurement visits, from their second antenatal clinic visit until their first postpartum clinic visit. ART initiation and antenatal follow-up takes place at the Gugulethu MOU according to standard provincial protocols.
- **Phase 3** of the study is a randomised trial of strategies for delivering ART to women during the postpartum period (the primary objective; n= up to 480). Women enrolled in Phase 2 who are breastfeeding their infants will be approached to participate in the trial at the end of the first routine postpartum clinic visit. Phase 3 will randomise women to one of two approaches to providing ART during the postpartum period to HIV-infected mothers who are breastfeeding:
  - Arm A: referral of women to their nearest general adult ART services at approximately 4-8 weeks postpartum (the current standard of care in this setting)
  - Arm B: continued receipt of ART in the antenatal clinic, as part of a MCH-focused ART service at the Gugulethu MOU that only refers women to general adult ART services after the end of breastfeeding and once infants' final HIV status is determined

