## **10. Analytic considerations**

The study is a multiphase evaluation, with the main component designed to compare the impact of two different ART management strategies on clinical, behavioural, acceptability and cost-effectiveness outcomes among HIV- positive ART-eligible pregnant women seeking antenatal care. The primary outcomes, to be assessed using a randomised trial design (Phase 3), are viral suppression and retention in care of mother and infant at 12 months postpartum. The study analysis is driven by two competing hypotheses:

- **Hypothesis 1:** Maintaining women in MCH-focused ART services during the postpartum period will result in a higher proportion of women retained in care and virally suppressed throughout the period of infant HIV exposure via breastfeeding, compared to referral of women to general adult ART services early postpartum.
- **Hypothesis 2:** Referral of women to general adult ART services earlier in the postpartum period will result in higher levels of retention on ART at 12 months postpartum, compared to maintaining women in MCH-focused ART services throughout the breastfeeding period.

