#### Data analysis

Data will be exported to Stata Version 12.0 (Stata Corporation, College Station, Texas) or R (Gnu Project) for analysis. All analyses will be carried out under supervision by the study statistician. All outcomes will be blinded to investigators until the data are cleaned and data analyses completed.

As described above, the primary analysis population (up to n=390) is all women enrolled into Phase 3 of the study who initiated ART during pregnancy after 1 July 2013 when the new provincial PMTCT guidelines were implemented. The subset of women in Phase 3 who initiated ART before this time (n=90, approximately) will contribute to a secondary analysis population comprised all women initiating ART in pregnancy and enrolled into Phase 3 during the study period (up to n=480).

For the primary objective, we hypothesize that women in the MCH-focused ART group will be more likely to be retained in care (defined as attending ART clinical appointments and/or medication refill visits in the window between 9 and 12 months postpartum) and maintain viral suppression (defined as <50 copies/mL, with secondary analyses at other thresholds) at 12 months postpartum, compared to women randomized to the general adult ART group. Comparisons of study groups at enrolment will be stratified by duration of ART during antenatal period (i.e., prior to randomization), and will examine demographic and HIV-related variables. Comparison of outcomes will be based on Fisher's exact test, comparing the proportion of women in each arm reaching the primary endpoint and its components; all statistical tests for the primary analysis will be two-sided at  $\alpha=0.05$ . Analyses will be by intention-to-treat, with secondary analyses stratified by duration of postnatal follow-up in the MCH-ART arm. The duration of viral suppression during the postpartum period will be defined as cumulative study time with a documented VL<50 copies/mL (with sub-analyses for <400 and <1000 copies/mL). Kaplan-Meier methods stratified by study group will be used to describe time to detectable viraemia and time to defaulting care, with proportional hazards models used to examine the independent influence of participant characteristics. Note that primary analyses will draw only on women enrolled into Phase 1 and initiating ART after 1 July 2013; women initiating ART before this time will be included as a secondary analysis population for selected analyses.

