Secondary objective 2.4 will be addressed through analyses of the association between demographic, psychosocial and clinical measures (including characteristics of antenatal ART use) on the primary outcome. Analyses will parallel the pure count and time-to-event methods described for the primary objective. In addition, we will use proportional hazards models to identify measures independently associated with the primary outcome and its constituents; variable selection will be based on directed acyclic graphs developed *a priori* to help distinguish causal intermediates from confounding variables (for instance, antenatal ART adherence may be a causal intermediate through which demographic or psychosocial characteristics influence the primary outcome, rather than a confounder). All regression analyses will include trial arm as a covariate; other aspects of model building and diagnostics will follow standard approaches. Outputs will be expressed as hazard ratios and 95% confidence intervals.

Comparison of secondary outcomes between the two postnatal ART services will employ both pure count and person-time methods, as described above. Patterns of women's missed visits during the postpartum period (objective 2.5.A) will be analysed according to the frequency of different numbers of missed/late visits, and the timing of the missed/late visits during the postpartum. Breastfeeding practices (objective 2.5.B) will be analysed according to the duration of exclusive breastfeeding from birth; the duration of mixed feeding; and the timing of final infant exposure to breastmilk. Maternal viral suppression (objective 2.5.C) will be analysed according to the frequency and timing of detectable viraemia (with cutpoints at <50 and <1000 copies/mL) as well as 'survival' to detectable viraemia through 12 months. Incidence of infant respiratory and/or diarrhoeal illness (objective 2.5.D) will be analysed using person-time methods; comparisons of infant growth parameters will use dependent (intra-child) and independent (between child) comparisons. Rates of mother-to-child transmission will be compared at 6 weeks and 12 months using pure count methods (objective 2.5.E).

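### Objective 2.4 applies proportional hazards models and hazard ratios to a 12-month yes/no outcome that has no event time

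*Protocol*

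**What the plan says.** The Study synopsis fixes the outcome at a time point: "The primary outcomes are (i) maternal HIV viral suppression, and (ii) maternal retention in ART services, at 12 months postpartum". Section 10, Data analysis, defines retention as "attending ART clinical appointments and/or medication refill visits in the window between 9 and 12 months postpartum" and suppression as a viral load below 50 copies/mL. It compares the arms with Fisher's exact test on the proportions reaching the endpoint and its components. The sample size table in section 10 is likewise built on two proportions at 12 months.

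For objective 2.4, which asks which characteristics of the women are independently associated with this outcome, the same section says:

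- "Analyses will parallel the pure count and time-to-event methods described for the primary objective";
- as an addition to those, "we will use proportional hazards models to identify measures independently associated with the primary outcome and its constituents";
- on adjustment, "All regression analyses will include trial arm as a covariate", while the rest of the model building and its diagnostics is left to usual practice;
- on reporting, "Outputs will be expressed as hazard ratios and 95% confidence intervals".

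The time-to-event endpoints that Data analysis names are time to detectable viraemia and time to defaulting from care, with survival to detectable viraemia listed again under objective 2.5.C. None is defined for the composite.

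**The concern.** A proportional hazards model needs a time for each event. The composite and its two 12-month components are states observed at, or in a window ending at, a fixed time. The model and effect measure named for objective 2.4 therefore do not belong to the outcome they are attached to.

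This matters because the proportional hazards model is the only regression named for the objective, so it alone carries the claim of independent association. An analyst following the text must either force a fixed-time outcome into a Cox model or substitute another endpoint without saying so. Two competent analysts could report different numbers under the same label. The hazard ratios would also be read as describing the primary outcome when they describe something else.

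**Working it through.** **Step 1. Is the primary outcome binary in the protocol's own arithmetic?** Inputs from section 10, Sample size considerations: 10% v 25%, two-sided alpha 0.05, 90% power, 1:1 allocation. I read 10% and 25% as failure proportions, as the control-arm assumption and the stated risk ratio of about 0.4 require (0.10/0.25 = 0.40). With mean proportion 0.175 and difference 0.15:

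- Uncorrected n per arm = [1.960·√(2·0.175·0.825) + 1.282·√(0.10·0.90 + 0.25·0.75)]² / 0.15² = (1.053 + 0.675)² / 0.0225 ≈ 132.8, so 133 per arm and 266 in total.
- With continuity correction, n' = (n/4)·[1 + √(1 + 4/(n·0.15))]² = (132.8/4)·(2.096)² ≈ 145.8, so 146 per arm and 292 in total.

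The stated figure is 292, and the other eight rows of the table also reproduce exactly with the correction. The calculation compares two proportions at a fixed time and involves no event count or follow-up time.

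**Step 2. What does a Cox model give if every time is set to 12 months?** Take the same 10% v 25% as two illustrative groups of 2,000, with 200 and 500 failures, all tied at 12 months.

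- Breslow ties: the score equation reduces to HR = (200/2000)/(500/2000) = 0.40, which is simply the risk ratio.
- Efron ties: the fitted HR is 0.37.
- Complementary log-log: ln(0.90)/ln(0.75) = 0.37.
- Odds ratio: (0.10/0.90)/(0.25/0.75) = 0.33.

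The hazard ratio is thus 0.40 or 0.37 by a software option, whereas the risk ratio and the odds ratio each have one value.

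**Step 3. What if the named time-to-event endpoints are substituted?** Set the two side by side for a woman who is viraemic at 6 months and suppressed and attending at 12 months. In time to detectable viraemia she is an event. On the primary outcome she is a success. The same holds for a woman who defaults early and is back in care by months 9 to 12. The protocol provides for such returns: under Identification of health care needs, women found to have defaulted are sent back to their ART service. A predictor of first failure need not be a predictor of status at 12 months.

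**Step 4. Does it matter how arm enters the legitimate Cox models?** Section 7 has Arm A referred at about 4 to 8 weeks and Arm B after breastfeeding ends, so proportional hazards for arm are doubtful. The protocol gives no default rates, so the hazards here are assumptions: piecewise constant with breaks at 1.5 and 5 months, followed to 12 months, with a true covariate hazard ratio of 2.0 and 20,000 women per scenario.

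| Assumed monthly hazards, A; B | Covariate HR, arm as covariate | Covariate HR, arm as stratum |
|---|---|---|
| 0.01, 0.05, 0.02; 0.01, 0.01, 0.02 | 1.99 | 1.98 |
| 0.01, 0.05, 0.01; 0.01, 0.01, 0.03 | 1.95 | 1.94 |
| 0.01, 0.06, 0.005; 0.01, 0.01, 0.04 | 1.95 | 1.95 |

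The covariate hazard ratios that objective 2.4 seeks move by about 0.01 or less.

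**The case against.** The best defence has four parts.

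- *The constituents have time-to-event counterparts.* Time to viraemia and time to default are named, and hazard ratios are proper for them. That stands. They are nevertheless different endpoints from the 12-month states (step 3), and the composite has no counterpart at all.
- *Count methods are kept.* They are, and the hazard models come in addition. A reader might infer that objective 2.4 cannot be answered on the primary outcome at all. The protocol does not support that, because unadjusted comparisons of the binary outcome remain planned. What is missing is an adjusted model that fits it.
- *This is detail for the statistical analysis plan.* Choosing among binary models would be, and so would handling arm as a stratum. Here, though, the protocol has already fixed a model and an effect measure that disagree with its own outcome definition, so this is not an omission.
- *The analysis is secondary.* That stands. Fisher's test and the sample size are untouched.

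A stronger reading is also tempting: that the design makes the arm effect reverse over time, so a single arm hazard ratio would mislead. Hypothesis 1 favours Arm B during breastfeeding, and Hypothesis 2 says that earlier referral "will result in higher levels of retention on ART at 12 months postpartum". But section 10 presents these as rival predictions, not as a joint forecast. Staggered transfer makes non-proportional hazards plausible without fixing any change of sign. Arm is only an adjustment covariate in objective 2.4, and the standard diagnostics promised there leave room for a proportionality check.

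**Conclusion.** The point holds in a limited form. For the 12-month composite and its 12-month components, the regression and effect measure named for objective 2.4 do not match the outcome. The result is either not uniquely defined (0.37 or 0.40 on the protocol's own 10% v 25%) or concerns first viraemia or default instead. The mismatch follows from the text alone. The numerical illustration uses the planning proportions as a stand-in for a contrast between subgroups of women, and its size would differ with other proportions.

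Doubt about proportional hazards for arm is a side issue: under the assumed hazards it changes the covariate hazard ratios by about 0.01 or less. No claim of a reversing arm effect is warranted. The correction is worth making but does not touch the trial's primary comparison.

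**What to change.** In section 10, Data analysis, rewrite the objective 2.4 regression text so that:

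1. associations with the 12-month composite, and with retention and suppression at 12 months, are estimated by a binary regression that includes arm, for example modified Poisson with robust variance, and reported as risk ratios with 95% confidence intervals;
2. proportional hazards models and hazard ratios are confined to the named time-to-event endpoints, time to detectable viraemia and time to defaulting from care, and are labelled as such rather than as analyses of the primary outcome;
3. optionally, arm is entered as a stratum in those Cox models, which avoids assuming proportional hazards for arm.

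The a priori causal diagrams for variable selection can stay as they are. The cost is a change of wording in the protocol, carried into the analysis plan. The data, sample size and software are the same.

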### **Secondary objectives**

- 2.1 To characterize the health status of the population of HIV+ pregnant women seeking antenatal care at the Gugulethu Midwife Obstetric Unit (MOU) including maternal and infant outcomes
- 2.2 To describe uptake and timing of services received throughout the PMTCT cascade, including antenatal ART initiation and follow-up, at the Gugulethu MOU
- 2.3 To examine whether there is variation in the impact of the two postpartum HIV care strategies on the primary outcome between subgroups of women according to their demographic, clinical and psychosocial characteristics, measured antenatally and postnatally.
- 2.4 To describe changes in women's clinical and/or psychosocial characteristics between the antenatal and postnatal periods, and investigate how these are independently associated with the primary outcome
- 2.5 To compare MCH-focused ART services to general adult ART services on:
  - a. Women's missed visits and loss to follow-up on ART up to 18 months postpartum
  - b. Breastfeeding practices, including duration of exclusive feeding and weaning patterns
  - c. Maternal viral suppression throughout the breastfeeding period as well as before and after cessation of breastfeeding
  - d. Infant health outcomes including growth parameters and incidence of respiratory and/or diarrhoeal illness
  - e. Rates of HIV transmission from mother-to-child at 6 weeks and 12 months postpartum
  - f. Acceptability of different strategies for delivering HIV care and treatment during the postpartum period
  - g. Cost-effectiveness in delivering HIV care and treatment during the postpartum period
  - h. Developmental scores of 1 year old infants

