#### General adult ART management strategy

Women and infants randomized to the general adult ART management strategy will receive postpartum ART services according to the local standard of care. Specifically, women will be referred from the MOU ART service to their nearest adult ART clinic at their first postpartum ART clinic visit, at around 6 weeks postpartum. The precise timing of this referral will depend on the scheduling of women's ART visits, and may take place between approximately 4 and 8 weeks after birth. Infants will be referred for routine infant care to local primary care clinics, following standard of care in this setting.

The specific facility women are referred to will be determined by their area of residence. For women who reside within Gugulethu itself, referral will be to the ART service at the Gugulethu CHC (located approximately 100 metres from the MOU; this applies to approximately 60-70% of women attending the MOU); the corresponding infant referral is to one of four primary care clinics in the local community. For women who live in other communities (with the Gugulethu MOU as their closest antenatal clinic, but not their closest ART clinic), referral will be to their nearest adult ART clinic, primarily facilities serving the communities of Philippi and Nyanga. All infants will be referred to their nearest routine infant follow-up service. Women may be referred to other facilities (e.g., in other parts of Cape Town or in the Eastern Cape) upon request.

In addition, midwives working in the MOU-ART service may opt to refer a woman to a higher level of medical care (e.g., if there is concern regarding ART toxicity) or on the basis of clinical or psychosocial grounds (if there are concerns regarding non-adherence). Reasons for deferred or alternate referral are documented in the clinical record.

On the day of referral, all women receive counselling on long-term ART adherence, the ongoing risks of MTCT through breastfeeding, and the need for repeat infant HIV testing. Following provincial protocols, referrals employ a Western Cape ART transfer form, completed in duplicate. The original form is sent with the patient, and the copy is retained in the patient's MOU folder. Patients are prescribed one month of treatment and advised to make an appointment at their referral clinic as soon as possible before their one-month ART supply is finished.

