#### MCH-focused ART management strategy

Women randomised to the MCH-focused ART management strategy will be retained in the MOU-ART service, along with their infants, throughout the period of breastfeeding, and referred to their nearest adult ART clinic (as described above) only after the end of breastfeeding. ART visits will be scheduled 1-2 monthly throughout this period. At each clinic visit during the postpartum period, mothers and infants will receive:

- Routine ART care, following local protocols
- Review of infant feeding practices specifically
- Routine infant health care (including infant weight monitoring, vaccination and early infant HIV diagnosis) with completion of the infant's Road-to-Health Card. This is the identical set of services to those provided through local primary care clinics; in all instances, there is referral to local paediatric services when required
- Ongoing PMTCT counselling, including messaging on ongoing transmission risk during the postpartum period; ART adherence; safe infant feeding practices; adherence to daily nevirapine prophylaxis (through 6 weeks postpartum per local guidelines); and the need for infant HIV testing at 6 weeks postpartum and again after cessation of breastfeeding

At each postpartum visit, mothers will be asked basic questions on infant feeding practices related to current feeding practice, plans for weaning and future feeding intentions. Mothers who are found to have not breastfed for at least 1 week before a clinic visit, and who do not state an intention to resume breastfeeding, will be eligible for referral out of the MOU ART service. Referrals out of the MOU ART service will follow the guidelines described above. For mothers who are referred out of the MOU, infants will be referred to their nearest routine infant follow-up service.

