### **Abstraction of routinely collected clinical information**

In addition to the study measures described above, chart reviews will be conducted in order to collect key data on participants regarding (a) antenatal and obstetric care and (b) ART initiation and follow-up. Permission to review clinical records of participants is included in informed consent documents for all participants.

- *Antenatal information* will be taken from MOU records, including the results of routine bloods (syphilis screening, ABO blood group), the number and timing of ANC visits, the results of prenatal ultrasound scan, and any evidence of antenatal complications including episodes requiring referral to specialist obstetric care.
- *PMTCT information*. Will come from antenatal and obstetric records, including: CD4 enumeration, dates and types of antiretroviral drugs received.
- *Obstetric information* will be abstracted from the records at the MOU or nearby obstetric hospitals. We will abstract the date and time of the onset of labour and rupture of membranes, the progress of labour and evidence of fetal distress, the date, time and mode of delivery; birth outcome; any PMTCT interventions received; Apgar scores at 1 and 5 minutes postpartum; neonate mass, head circumference and length, and placental weight.
- *ART initiation and follow-up data* will be abstracted at the end of the study from routine clinical care records maintained by the general ART and MOU-ART services. Items to be abstracted from these clinical records include: date of initial presentation to the ART service; pre-ART clinical history, examination and laboratory investigations (including TB-related history and WHO staging); date of ART initiation; dates of routine follow-up visits post-ART initiation and major clinical events, including clinical findings that may suggest opportunistic infections, ART side effects, drug toxicities; pharmacy dispensing & refill information; and missed follow-up visits and retention in care. Information through 18 months postpartum will be abstracted on all participants from the relevant clinical records at either the general ART or the MOU-ART service, as appropriate.

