| ART initiation & follow-up                      |                                                    | X                                                        | X                                                 | X                                                     | X                                                                  | X                               | X                               |                                 | X                                | X                                 |
| Antenatal & obstetric information               | X                                                  | X                                                        | X                                                 | X                                                     |                                                                    |                                 |                                 |                                 |                                  |                                   |
| Pharmacy ART dispensing records                 |                                                    | X                                                        | X                                                 | X                                                     | X                                                                  | X                               | X                               | X                               | X                                | X                                 |
| Maternal laboratory test results    | X                                                  | X                                                        |                                                   |                                                       |                                                                    |                                 | X                               |                                 | X                                | X                                 |

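### Objective 2.5.A counts missed visits recorded by clinics, a measure likely to under-detect failed or late linkage after referral, and to do so more in Arm A, which is referred earlier

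*Protocol*

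**What the plan says.** Objective 2.5.a (Secondary objectives) compares the arms on "Women's missed visits and loss to follow-up on ART up to 18 months postpartum". Under Data analysis, the missed-visit part "will be analysed according to the frequency of different numbers of missed/late visits" and by when in the postpartum period those visits fall. Secondary outcomes in general "will employ both pure count and person-time methods, as described above". No visit schedule against which a visit counts as missed or late is given.

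The source is named in the section on abstraction of routine clinical information. Items taken from the general ART or MOU-ART records, through 18 months postpartum, include "pharmacy dispensing & refill information; and missed follow-up visits and retention in care". The schedule of measurements lists "Pharmacy ART dispensing records" for every column from the second antenatal visit to 18 months; its footnote 8 says that abstraction happens at the end of the study.

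The arms reach the general ART service as follows:

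- **Arm A:** referral at about 4-8 weeks. The woman takes the original transfer form with her, receives one month of treatment and is "advised to make an appointment at their referral clinic as soon as possible before their one-month ART supply is finished".
- **Arm B:** while she is breastfeeding, "ART visits will be scheduled 1-2 monthly throughout this period" at the MOU. Once breastfeeding has ended she is referred by the same procedure as in Arm A.

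**The concern.** A clinic can most readily record a missed visit when it was expecting the woman. During breastfeeding in Arm B the MOU sets the appointments, so non-attendance leaves a trace. After referral in either arm, nothing in the protocol tells the receiving clinic to expect her: she carries the form and books for herself. If she never goes, or goes months late, the receiving clinic may hold no record of a missed visit for that time.

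The gap exists in both arms, but not for equal time. Arm A enters it at about 6 weeks, Arm B after weaning. Time spent in the MOU service before referral is exactly what the trial varies, so the under-detection is differential. At stake is a secondary comparison in which the arm that leaves more due visits unattended could show the lower count of missed visits.

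**Working it through.** The protocol states no figure for missed visits or linkage, so there is nothing to reproduce on this point. The sample size table concerns the primary endpoint and does not bear on it.

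**Inputs from the protocol.** Referral in Arm A at around 6 weeks (1.5 months). Visits 1-2 monthly in both services. Most women expected to stop breastfeeding by 6 months (Background), taken here as the time of Arm B referral. Horizon 12 months, then the objective's 18 months.

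**Assumptions, not in the protocol.** Per-visit miss probability m = 0.10, equal in both services. Share never linking u = 0.20 after any referral, with a range of 0.05 to 0.30.

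**Notation, monthly visits to 12 months.** V = 12 − 1.5 = 10.5 visits due. In Arm B, v1 = 6 − 1.5 = 4.5 fall before referral and v2 = 12 − 6 = 6 after it.

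*Recorded visits only (an unlinked woman contributes nothing after referral)*
- Arm A: (1 − u)·V·m = 0.80 × 10.5 × 0.10 = 0.84
- Arm B: v1·m + (1 − u)·v2·m = 0.45 + 0.48 = 0.93

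*Visits due (an unlinked woman's due visits count as missed)*
- Arm A: 0.84 + u·V = 0.84 + 2.10 = 2.94
- Arm B: 0.93 + u·v2 = 0.93 + 1.20 = 2.13

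The recorded count puts Arm A lower by 0.09 visits per woman; the due-visit count puts it higher by 0.81.

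**Range of u (monthly visits, m = 0.10, Arm B referred at 6 months)**

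| u | Recorded A | Recorded B | Due A | Due B |
|---|---|---|---|---|
| 0.05 | 1.00 | 1.02 | 1.52 | 1.32 |
| 0.20 | 0.84 | 0.93 | 2.94 | 2.13 |
| 0.30 | 0.735 | 0.87 | 3.885 | 2.67 |

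**Other settings at u = 0.20**
- Two-monthly visits and m = 0.20: V = 5.25, v1 = 2.25, v2 = 3. Recorded 0.84 against 0.93; due 1.89 against 1.53.
- Arm B kept at the MOU to 12 months: Arm B is 10.5 × 0.10 = 1.05 on both counts, against 0.84 and 2.94 in Arm A.
- Horizon 18 months: V = 16.5, v2 = 12. Recorded 1.32 against 1.41; due 4.62 against 3.81.

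**Why the sign is stable.** With equal m and u, recorded B − A = u·m·v1, and due A − B = u·(1 − m)·v1. Both are positive whenever some women fail to link and Arm B spends any time at the MOU after Arm A has been referred.

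**If non-linkage differs by arm.** Recorded B − A becomes m·(uA·V − uB·v2). The lean towards Arm A then needs uB/uA below V/v2, which is 10.5/6 = 1.75 at 12 months and 16.5/12 = 1.375 at 18 months.

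**The case against.** The strongest reply is that the protocol never defines a missed or late visit. An analysis plan could count visits due on the 1-2 monthly schedule, or date lateness from the end of the one-month transfer supply; the dispensing data for this are collected. A woman who books and does not attend may also be recorded as missed, and one who links months late could be classed as late.

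This stands in part. A reader might infer that an unlinked woman necessarily has no visit to miss. The documents do not say so; it is an inference from the self-booked appointment and the clinic-record source. But the protocol goes further than leaving a detail open: it names the measure and lists "missed follow-up visits and retention in care" among the items to be taken from the records. Read together, these point to the recorded count.

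A reader might also infer that the blind spot belongs to Arm A alone. It does not. Arm B women are referred by the same procedure, many perhaps by 6 months, so much of an 18-month horizon carries the same gap in both arms. That leaves the recorded difference small (0.09 in the illustration) but does not change its direction under equal rates.

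Finally, a reader might infer that poor linkage in Arm A could go unseen in the trial. The documents do not support that. Objective 2.5.a also covers loss to follow-up, Kaplan-Meier methods describe time to defaulting care, and the retention component of the primary outcome requires attendance between 9 and 12 months. A woman who never links registers on all three.

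**Conclusion.** The concern holds for one secondary measure. A count of recorded missed or late visits is likely to under-detect failed and late linkage after referral, and more so in Arm A because it is referred earlier. On the assumed rates, recorded missed visits to 12 months are 0.84 in Arm A against 0.93 in Arm B, while visits due and not attended are 2.94 against 2.13.

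The sizes are illustrative. They rest on assumed miss and non-linkage rates, on the same miss rate in both services, on similar non-linkage after early and late referral, and on reading the measure as a count of recorded missed visits. With unequal miss rates the ranking need not reverse. The primary outcome is untouched; the practical risk is a 2.5.A result that contradicts the retention and defaulting results for reasons of record keeping.

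**What to change.** Define 2.5.A independently of booking, for every randomised woman in both arms, in one of two ways:

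- number, length and timing of gaps in dispensed ART; or
- visits due on the 1-2 monthly schedule and not attended.

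After any referral, in either arm, start the clock at the end of the one-month transfer supply and count failure to link as missed. Use the visit and dispensing dates already abstracted at the end of the study. Report by arm the proportion linked after referral, and keep recorded missed visits as a description only.

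The cost is a change of wording and some more analysis work, with no new type of data. One caution: women may be referred elsewhere in Cape Town or to the Eastern Cape, and some will have no traceable record. Counting all of them as without ART to 18 months would tend to count against the arm referred earlier. Report them separately by arm, with a sensitivity analysis.
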